### Data collection

Laboratory parameters will be used for validity and safety assessments (see Fig. 2 for details). The central laboratory will provide all the appropriate materials needed by the research centers for sample collection, processing, packaging, and transportation. Before starting the clinical study, a laboratory manual will be provided to center researchers, containing a detailed description. Insulin, glucagon, and GLP-1 will be measured by the central laboratory, while other assays are carried out by the sub-centers, according to the unified standard provided by the coordinator.

Before blood collection, subjects will sit for 5 min. A tourniquet will be used for up to 2 min. For serum insulin assay, 5 ml whole blood will be taken while fasting, and 30 min and 2 h after glucose intake. This will be centrifuged for 2 h, and the separated serum will be collected into cryopreservation tubes. For glycosylated hemoglobin (HbA1c) measurement 2 ml whole blood will be obtained and placed into blood collection tubes containing EDTA. For GLP-1 and glucagon assay, 5 ml blood will be obtained using vacuum blood collection tubes containing EDTA and aprotinin, after fasting, and 30 min and 2 h after a meal, and the centrifuged serum will be collected into cryopreserved tubes for storage at − 20 °C. Stool specimens the size of soybeans will be placed into dry, sterile collection tubes, and sent to the analysis center within 24 h for cryopreservation.

Prior to undergoing an oral glucose tolerance test (OGTT) subjects will consume a normal diet (with carbohydrate content no less than 150 g) for at least 3 days. After 10–12 h of fasting, they will be required to empty their bladder and an initial blood sample will be obtained. Then they will drink 75 g anhydrous glucose dissolved in 300 ml water over approximately 5 min, and the time of ingestion will be recorded. Further blood samples will be then obtained after 30 min and 2 h.

### Statistical methods

Because no previous studies of treatment with bifidobacteria have been conducted, this represents a pilot study. Sample size was estimated using NCSS PASS 11 (NCSS LLC, Kaysville, UT, USA) software, and it was planned that 300 subjects would be enrolled. The detailed statistical methods are described below.

Superiority hypothesis: in case of occurrence of superiority of either the berberine, *Bifidobacterium* or combination group, the test will be deemed successful, with the bilateral test level for α = 5% (no correction), and for β = 20% (power 80%).

The primary observation indicator in this study was the absolute value of fasting plasma glucose (FPG) compared with baseline after 16 weeks of treatment. The berberine sample size was estimated with reference to the STOP-NIDDM study [4] and Yifei Zhang’s study [11] on the use of berberine to treat type 2 diabetes with hyperlipidemia. In this study, berberine treatment decreased FPG by 1.45 ± 0.85 (standard deviation (SD)) mmol/L, while FPG in the placebo control group decreased by 0.6 ± 1.2 mmol/L. With a difference in FPG between the berberine and placebo groups of 0.85 mmol/L, the estimated pooled variance was 2, and the estimated sample size was 44.

The bifidobacteria sample size was estimated based on a decrease in FPG of 1.2 ± 1.1 mmol/L, and a decrease in FPG in the placebo control group of 0.6 ± 1.0 mmol/L. Assuming that the difference in FPG decrease between the berberine and placebo groups was 0.6 mmol/L, and the estimated pooled variance was 2, the estimated sample size was 88 persons in a single group. Allowing for some expulsions, the final sample size for each group was determined to be 50 for the berberine group, 100 for the *Bifidobacterium* group, 50 for the combination group, and 100 for the placebo control group, giving a total sample size of 300.

The primary analysis population will undergo at least one trial drug treatment and have at least one follow-up record comprising a full analysis set (FAS) and will be analyzed on an intention-to-treat (ITT) basis, including all randomized patients. All support analyses will be based on per-protocol sets (PPSs), and the security endpoint analysis will be based on a safety set (SS). The study will not incorporate a planned mid-point analysis.

All data will be analyzed using SAS 9.3 (SAS institute Inc, Cary, NC, USA) software using pre-programmed algorithms. Quantitative indices recorded will include the mean ± SD, median, maximum and minimum values; qualitative or grade indices will be recorded using a frequency distribution table. Two-sided tests will be used in all cases, and *P* ≤ 0.05 will be considered to be statistically significant. Fisher’s exact probability test will be used to compare the expulsion rates between the groups.

Validity analysis will be based on the FAS, using a covariance analysis model, with the main and secondary efficacy index baseline values being the covariates in the model, and the central effect serving as the fixed-effect term. The least squares estimates will be used to calculate the corrected mean and the 95% confidence intervals for changes in each group, and the 95% confidence interval of the Dunnett corrected mean difference between the test and placebo groups will be used to fit a covariance analysis model with central and group interactions to test the consistency among study centers. The applicability of this covariance analysis model will be investigated at the level of α = 0.10. Unless otherwise specified, the method of Carrying Forward (last observation carried forward, LOCF) will be used for sensitivity analysis of each validity analysis.

Security analysis will be based on a SS. Safety endpoints will be analyzed and adverse events aggregated. The continuous variables or frequency counts and percentage in safety and tolerability endpoints will be analyzed using descriptive statistics. The relative indices for hypoglycemic events and changes in weight will be compared between groups according to general principles.

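### The 80% power printed with the any-arm success rule is a per-comparison, uncorrected figure: it is neither the power of that rule nor, at the plan's variance of 2, of the Bifidobacterium contrast under the Dunnett correction

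*Protocol article*

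**What the plan says.** All of this is in the Statistical methods section of the protocol article.

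- **Success rule and error rates.** The superiority paragraph lets a win by any one of the three active arms count as success. It then sets the error rates in the same sentence: "the test will be deemed successful, with the bilateral test level for α = 5% (no correction), and for β = 20% (power 80". The closing figure is a percentage.
- **Berberine sizing.** The assumed advantage of berberine over placebo is 0.85 mmol/L. The result is given as follows: "the estimated pooled variance was 2, and the estimated sample size was 44".
- **Bifidobacterium sizing.** A difference of 0.6 mmol/L, again with variance 2, gives 88 in a group. The sentence names berberine where the context requires Bifidobacterium; it is read here as Bifidobacterium.
- **Combination.** No effect is stated and no calculation is shown.
- **Allocation.** The numbers are raised to cover losses: "the final sample size for each group was determined to be 50 for the berberine group". The combination arm also has 50, and the Bifidobacterium and placebo arms have 100 each.
- **Analysis.** A covariance model with baseline as covariate, reporting "the 95% confidence interval of the Dunnett corrected mean difference between the test and placebo groups".

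**The concern.** The one power figure sits in the sentence that defines success as a win by any of three arms, so a reader will take it as the power of that rule. The calculations beneath it concern something else: two stand-alone comparisons, each with equal groups and an uncorrected 5% level. The planned trial gives three arms a chance to succeed, sets the two smaller arms against a placebo arm twice their size, and reports Dunnett-corrected contrasts.

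Two misreadings are at stake.

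- A declared success could rest on berberine only. If Bifidobacterium had no effect and the combination matched berberine, the uncorrected rule would still succeed about 98% of the time.
- A null Bifidobacterium result could be read as coming from a test with 80% power, when the Dunnett-corrected contrast has less than that at the plan's own variance. The Bifidobacterium and placebo arms together are 200 of the 300 patients.

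**Working it through.** **Inputs from the Statistical methods section.** Differences 0.85 (berberine) and 0.6 (Bifidobacterium) mmol/L; variance 2; two-sided 5%; power 80%; allocation 50/100/50/100 (berberine/Bifidobacterium/combination/placebo).

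**Assumed.** Evaluable numbers of 44/88/44/88, because 44/50 = 88/100 = 88%. A combination effect between 0 and 0.85 mmol/L, because none is given.

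**1. Reproduce the plan's figures.** With n per group = 2 × variance × (1.960 + 0.842)² / difference²:

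- Berberine: 2 × 2 × 7.849 / 0.7225 = 43.5, rounded up to 44.
- Bifidobacterium: 2 × 2 × 7.849 / 0.36 = 87.2, rounded up to 88.

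Both match. The 80% is therefore the power of an equal-group, uncorrected, two-arm test.

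**2. Power per contrast at the planned allocation.** SE = √[2 × (1/n₁ + 1/n₀)] and power ≈ Φ(difference/SE − c). The critical value c is 1.97 uncorrected. For Dunnett with three comparisons and these group sizes it is 2.38, obtained by simulation.

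| Contrast with placebo | n | SE | difference/SE | Uncorrected | Dunnett |
|---|---|---|---|---|---|
| Berberine | 44 vs 88 | 0.261 | 3.26 | 90% | 81% |
| Berberine | 50 vs 100 | 0.245 | 3.47 | 93% | 86% |
| Bifidobacterium | 88 vs 88 | 0.213 | 2.81 | 80% | 67% |
| Bifidobacterium | 100 vs 100 | 0.200 | 3.00 | 85% | 73% |

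Simulation gives the same values to the nearest per cent.

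**3. Power of the any-arm rule.** This was simulated with 1,000,000 draws of three t statistics sharing one placebo arm, variance 2, at 44/88/44/88. A win means superiority beyond the two-sided critical value.

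| Assumed combination effect (mmol/L) | Uncorrected | Dunnett |
|---|---|---|
| 0 | 95.5% | 89% |
| 0.6 | 96.8% | 91% |
| 0.85 | 98.5% | 95% |

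At 50/100/50/100 the ranges are 97.3–99.3% uncorrected and 93–97% with Dunnett.

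**4. Any-arm rule with Bifidobacterium inert (44/88/44/88).** With the combination equal to berberine, success is declared 97.7% of the time uncorrected and about 93% with Dunnett.

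**5. Sensitivity to the variance.** The printed SDs give (0.85² + 1.2²)/2 = 1.08 and (1.1² + 1.0²)/2 = 1.105, so about 1.1 rather than 2. At 1.1, the Bifidobacterium contrast under Dunnett has SE √[1.1 × 2/88] = 0.158, ratio 3.79 and power 92%. At 100 per arm, SE is 0.148, ratio 4.05 and power 95%. Berberine at 44 vs 88 has about 98%.

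**The case against.** **The arithmetic is right.** The inputs give 44 and 88 exactly, and the error rates can be read as per-comparison settings feeding two pairwise calculations. This stands: nothing is miscalculated. But on that reading the sentence still attaches the figure to an any-arm rule, and the Bifidobacterium contrast still loses its 80% if Dunnett governs.

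**Power above target harms nobody.** Also true. An any-arm figure in the nineties, or 90% for berberine against a larger placebo arm, is no shortfall. The problem is what a reader would conclude from the 80%.

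**The 67% is conditional.** It needs Dunnett to govern the decision, only 88 analysed per arm, variance 2, and nothing gained from the baseline covariate. The full analysis set is described as including all randomized patients, which points towards 100 per arm and 73%. Dunnett power would reach 80% at a residual variance of about 1.53 with 88 per arm, or about 1.74 with 100. The documents give no baseline correlation, so the gain cannot be sized. All of this stands, and is why a range is given.

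**Stronger readings that the article does not support.**

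- A reader might infer that the rule has 96–98% power while the Bifidobacterium contrast has 67%. No single reading gives both: uncorrected, Bifidobacterium keeps its printed 80% at 88 per arm; under Dunnett, the any-arm figure falls to 89–95%.
- A reader might infer that a successful trial would say nothing about Bifidobacterium. The success label would not, but corrected intervals for each test group against placebo are planned, so a separate Bifidobacterium result will exist.
- A reader might infer that the Bifidobacterium contrast is definitely underpowered. At the variance implied by the printed SDs it is not.

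**Conclusion.** The point holds as a misattributed power figure, not as an arithmetic error. The 80% belongs to two uncorrected equal-group comparisons. It does not describe the any-arm rule under either critical value. It also does not describe the Bifidobacterium contrast under the planned Dunnett intervals, where the plan's variance of 2 gives 67–73% according to whether 88 or 100 per arm are analysed.

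The shortfall for Bifidobacterium depends on Dunnett governing, on variance 2 and on no gain from baseline adjustment. The misfit between the 80% and the any-arm rule depends on none of these: a smaller variance only raises the any-arm power further. The root is that the section says both that the 5% level is uncorrected and that the contrasts are Dunnett-corrected; until that is settled, no single power statement can be right.

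**What to change.** 1. Reconcile the uncorrected 5% level in the superiority paragraph with the Dunnett correction in the analysis paragraph, and say which one decides superiority.
2. Remove the 80% from the any-arm sentence.
3. State power for each contrast with placebo at 50/100/50/100 under the chosen correction, giving the number analysed, the variance and any assumed gain from the baseline covariate. With Dunnett, variance 2 and no such gain, this is about 81–86% for berberine and 67–73% for Bifidobacterium. Explain the choice of 2 over the roughly 1.1 implied by the printed SDs, since the Bifidobacterium figure turns on it.
4. For the combination, state an assumed effect and the power that follows.
5. Replace the single success declaration with one conclusion per arm, so that a berberine win is not reported as success for Bifidobacterium.

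The cost is rewording of the sample-size and success paragraphs, with no extra patients or procedures. The downside is a less favourable stated power for Bifidobacterium if Dunnett and variance 2 are kept.

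### The success rule (any of three arms, no multiplicity correction) and the Dunnett-corrected intervals can disagree, and the protocol does not say which decides

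*Protocol article*

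**What the plan says.** Everything below is in the Statistical methods section of the protocol article.

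- **Success rule.** It begins "Superiority hypothesis: in case of occurrence of superiority of either the berberine" and goes on to list the Bifidobacterium and combination groups. One superior arm is enough. The sentence continues: "the test will be deemed successful, with the bilateral test level for α = 5% (no correction"), and gives the planning error as "for β = 20% (power 80"%).
- **Sample size.** For berberine: "With a difference in FPG between the berberine and placebo groups of 0.85 mmol/L, the estimated pooled variance was 2", giving 44. For Bifidobacterium, a difference of 0.6 mmol/L with the same variance gives 88 per group. With an allowance for expulsions the groups become 50 berberine, 100 Bifidobacterium, 50 combination and 100 placebo.
- **Analysis.** "Two-sided tests will be used in all cases", with P ≤ 0.05 as the significance threshold and no adjusted level named. The covariance analysis is also to give "the 95% confidence interval of the Dunnett corrected mean difference between the test and placebo groups". That sentence then runs on into the centre-by-group interaction model, so the purpose of the Dunnett interval is unclear.

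**The concern.** The success rule and the Dunnett intervals concern the same three comparisons with one placebo group, but they set different thresholds. With three chances to win and no correction, 5% is the error rate of each comparison and not of the trial. With Dunnett, the trial-level error is 5%, but each comparison faces a stricter threshold than the one used for the sample size.

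Two things are at stake. The report could declare success on an unadjusted p-value while the Dunnett interval for that arm includes zero. And if the choice of rule stays open until group results are known, the results could drive it.

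**Working it through.** **1. Reproduce the planned sample sizes.** Two means, 1:1, normal approximation, two-sided 5%, 80% power, variance 2: n per group = 2 × 2 × (1.960 + 0.842)² / d², where (1.960 + 0.842)² = 7.849.

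- d = 0.85: 4 × 7.849 / 0.7225 = 43.5, so 44.
- d = 0.60: 4 × 7.849 / 0.36 = 87.2, so 88.

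Both match the protocol. A Bonferroni level of 0.05/3 would give 58 and 117, and a one-sided 5% test 35 and 69. Planning therefore used the uncorrected two-sided 5%.

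**2. Error rate if the uncorrected rule decides.** The three comparisons share the placebo group, so their test statistics are correlated: ρ = √[nᵢ/(nᵢ+n₀)] × √[nⱼ/(nⱼ+n₀)]. With 50/100/50 against 100:

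- berberine with Bifidobacterium: √(50/150) × √(100/200) = 0.408; the same for combination with Bifidobacterium;
- berberine with combination: √(50/150) × √(50/150) = 0.333.

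Simulating this trivariate normal 4 million times with all three nulls true and a critical value of 1.96 gives:

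| Event | Three arms, uncorrected | Single comparison |
|---|---|---|
| At least one significant result, either direction | 13.2% | 5% |
| At least one significant result in favour of active treatment | 6.6% | 2.5% |

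The inflation is about 2.6-fold in both rows (13.2/5 and 6.6/2.5).

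**3. Where the rules disagree.** The 95th percentile of the largest absolute statistic in the same simulation is about 2.37, a nominal two-sided p of about 0.018. An arm with p between about 0.018 and 0.05 passes the uncorrected rule, yet its Dunnett 95% interval includes zero.

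**4. Power at the Dunnett threshold.** Power = Φ(d / √[variance × (1/n₁ + 1/n₀)] − c), with c = 1.960 uncorrected and 2.366 for Dunnett. At variance 2:

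| Comparison with placebo | d / SE | Uncorrected | Dunnett |
|---|---|---|---|
| Berberine, 44 v 88 | 0.85/0.261 = 3.26 | 90% | 81% |
| Berberine, 50 v 100 | 0.85/0.245 = 3.47 | 93% | 87% |
| Bifidobacterium, 88 v 88 | 0.60/0.213 = 2.81 | 80% | 67% |
| Bifidobacterium, 100 v 100 | 0.60/0.200 = 3.00 | 85% | 74% |

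At the Dunnett level, 80% power with 1:1 groups would need 57 and 115 per group, against the planned 44 and 88.

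**5. Dependence on the variance.** The SDs quoted for Bifidobacterium and placebo, 1.1 and 1.0, imply a variance of (1.21 + 1.00)/2 = 1.105, not 2. At 88 v 88, d / SE is then 0.60/0.158 = 3.79, and power under Dunnett is Φ(3.79 − 2.37) = 92%.

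**The case against.** - **The no-correction remark may be a planning input only.** It stands beside the power figure, and step 1 shows that the sample sizes were computed that way. Dunnett is also the only method named for the differences from placebo. If Dunnett decides, familywise error is controlled and neither 13% nor 6.6% arises. This stands as a possible reading, so the error rates are conditional. It does not settle the matter: the remark is attached to the definition of success, and P ≤ 0.05 is applied throughout.
- **13% is not the chance of a false trial success.** A reader might infer that it is. The protocol does not support that, because success requires superiority and a significantly worse arm does not count. The figure for false success is 6.6%.
- **The 80% power is not lost across the board.** A reader might infer that Dunnett undermines the whole power statement. It does not. Berberine keeps at least 81% at variance 2. The chance that at least one of berberine and Bifidobacterium wins under Dunnett is about 90% at 44/88/88 and 93% at 50/100/100, before the combination arm is counted. Only the Bifidobacterium comparison falls short, and only if the variance is near 2.
- **The study is called a pilot, and the absence of correction is disclosed.** This lowers the urgency somewhat. But the protocol still sets a formal superiority rule with a power target, and disclosure does not reconcile two conflicting rules.

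**Conclusion.** The contradiction is in the printed text and concerns how the primary outcome decides trial success. The two rules give opposite answers for nominal p-values between about 0.018 and 0.05. If the uncorrected rule decides, two-sided familywise error is about 13% instead of 5%, and the chance of a false superiority claim is about 6.6% instead of 2.5%. These figures assume that no arm has an effect, that group sizes are as planned, and that the statistics are approximately normal.

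If Dunnett decides, error is controlled, but the stated 80% power does not hold for Bifidobacterium at the plan's variance of 2 (67% to 74%). That shortfall rests on a variance the protocol's own SDs do not support; at about 1.1 it disappears.

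**What to change.** Before unblinding:

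1. State that success for an arm requires a Dunnett-adjusted two-sided p-value of 0.05 or less from the planned covariance analysis. Equivalently, the Dunnett 95% interval against placebo excludes zero in the favourable direction. Trial success is then at least one such arm.
2. Delete the no-correction remark, or confine it explicitly to the sample size calculation.
3. Separate the Dunnett sentence from the centre-by-group interaction model.
4. Restate power for each comparison at the Dunnett level, giving the group sizes and variance used. At variance 2 this is about 81% to 87% for berberine and 67% to 74% for Bifidobacterium. Note alongside that a variance of about 1.1 gives Bifidobacterium about 92% at 88 v 88.

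The cost is a few sentences and a less favourable stated power for Bifidobacterium. No extra patients are needed. Recruitment is still under way, and the protocol places confirmation of the analysis plan before the first unblinding, so there is time to do this.

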### Blinding and unblinding procedures

Because the two research drugs have different specifications and appearance, double-blind dual simulation will be selected as the method of blinding. The test and placebo drugs will be provided by the coordinating center in identical internal and external packaging.

A two-level blinding design will be used, with the first level being by group (groups A, B, C, and D) according to case number, and the second level by treatment (berberine, *Bifidobacterium*, combination and control). The random code list will be created by a statistical agency, the two-level treatment codes will be sealed separately in duplicate, with a copy being kept by each of the statistical agency and the central coordinator, and the treatment code will be not opened during the study. The study would have been considered invalid if any treatment code disclosure arose from any non-prescribed circumstances and if it affected the objectivity of the data obtained from the study.

A two-phase unblinding method will be adopted. When all of the CRFs have been entered into the database, the first unblinding (identifying groups A, B, C, and D) will be carried out after the blind review, data locking, and statistical analysis plans will be confirmed. The second unblinding will be conducted when the statistical analysis report is completed, to identify subjects in the berberine, *Bifidobacterium*, combination and control groups.

Each coded test drug will have a corresponding emergency letter, describing the subject’s medication, treatment methods, and the organization to which requests for emergency unblinding should be immediately reported. Emergency letters will be sealed and issued to the research center with the corresponding numbers, where they are preserved and not opened unless necessary. In the case of an emergency (for example, a severe adverse reaction), when the type of medication being administered must be known for the effective treatment of the subject, the researcher could access the appropriate letter. In this instance the identity of the opener, the opening date, and the reasons for doing so will be recorded on the CRF. Once unblinded, the subjects will withdraw from the trial, and be treated as expulsion cases. All emergency letters and CRFs will be collected at end of the trial for blind review.

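### The primary population is called intention-to-treat with all randomised patients, yet entry needs a dose and a follow-up record; the default sensitivity check, LOCF, cannot repair this

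*Protocol article*

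**What the plan says.** All of this is in the Protocol article.

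- **Primary population (Statistical methods).** Entry requires at least one treatment with trial drug and "at least one follow-up record comprising a full analysis set (FAS) and will be analyzed on an intention-to-treat (ITT) basis, including all randomized patients".
- **Efficacy model (Statistical methods).** "Validity analysis will be based on the FAS, using a covariance analysis model", adjusted for baseline and centre. The primary outcome is FPG at 16 weeks against baseline (Table 1).
- **Missing data (Statistical methods).** Unless something else is specified, "the method of Carrying Forward (last observation carried forward, LOCF) will be used for sensitivity analysis of each validity analysis". No method is named for a missing week-16 FPG in the primary model.
- **Other efficacy sets (Statistical methods).** Supporting analyses use per-protocol sets.
- **Emergency unblinding (Blinding and unblinding procedures).** "Once unblinded, the subjects will withdraw from the trial, and be treated as expulsion cases". The article does not say whether these patients remain in the full analysis set (FAS).

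**The concern.** One sentence gives two definitions of the primary population. Two programmers working from it could build different primary datasets, and a published claim of intention-to-treat could describe an analysis that left out randomised patients after allocation. Such exclusions are harmless only if they are unrelated to treatment and outcome. The unblinding route gives some reason for doubt, since the example trigger is a severe adverse reaction.

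A sensitivity analysis is where a reader would look for reassurance. The one prescribed by default makes a single fixed assumption about what happens after dropout and does not reach the patients whom the FAS leaves out. If it agreed with the primary result, the reader would learn little about how far that result depends on the missing data.

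**Working it through.** **1. Can both descriptions hold?** They coincide only if every randomised patient takes drug and has a follow-up record. The plan does not expect full retention: the sample size is raised to allow for expulsions, and expulsion rates are to be compared between groups by Fisher's exact test. Nothing elsewhere in the article resolves the conflict.

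**2. Does any other named efficacy analysis keep everyone?** The ANCOVA uses the FAS. Per-protocol sets are normally narrower still. LOCF needs a post-baseline value; carrying the baseline value forward would be a different rule, and none is named. So only the words "will be analyzed on an intention-to-treat (ITT) basis, including all randomized patients" point to an all-randomised analysis.

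**3. The plan's own sample sizes.** Inputs from Statistical methods: variance 2, two-sided 5%, power 80%, differences 1.45 − 0.6 = 0.85 and 1.2 − 0.6 = 0.6 mmol/L. Formula: n per group = 2σ²(z₀.₉₇₅ + z₀.₈₀)²/δ², with (1.960 + 0.842)² ≈ 7.85.
- Berberine: 2 × 2 × 7.85/0.85² ≈ 43.5, so 44, as stated.
- *Bifidobacterium*: 2 × 2 × 7.85/0.6² ≈ 87.2, so 88, as stated.

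**4. Implied loss.** 1 − 44/50 = 1 − 88/100 = 12%. The article states no rate. Applied to all four arms, which is an assumption, 12% is 36 of 300; a low value of 2% would be 6.

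**5. LOCF illustration (assumption).** Let a share p of an active arm stop, carry forward the full assumed fall, and in truth revert to the placebo fall, with no offset in the placebo arm. LOCF then reports the full fall, while the true arm mean is lower by p × δ.

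| p | Berberine (δ = 0.85) | *Bifidobacterium* (δ = 0.6) |
|---|---|---|
| 2% | 0.02 × 0.85 = 0.017 | 0.02 × 0.6 = 0.012 |
| 12% | 0.12 × 0.85 = 0.102 | 0.12 × 0.6 = 0.072 |

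Units are mmol/L. In each case the error is the share p of the assumed effect.

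**6. FAS exclusion illustration (assumption).** If excluded patients' FPG falls by g less than that of retained patients, the FAS difference minus the all-randomised difference is (d_active − d_placebo) × g, where d is the share excluded.
- 12% active, 4% placebo: 0.08 × 0.5 = 0.04 up to 0.08 × 1.45 = 0.12 mmol/L overstated.
- Equal shares and equal g: zero.
- 4% active, 12% placebo: the same sizes with the sign reversed.

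The sign depends on inputs that the article does not give.

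**7. Power.** At variance 2, power is 0.85 for 100 v 100 (δ = 0.6) and 0.93 for 50 v 100 (δ = 0.85). With 12% lost (88 v 88 and 44 v 88) it is 0.80 and 0.90. The issue is definition and robustness, not power.

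**The case against.** The best defence is that this is a condensed article. The statistical analysis plan is to be confirmed before the first unblinding, LOCF applies only where nothing else is specified, and a set requiring a dose and a follow-up record is common practice under the FAS label. On that view the defect is loose wording. This stands in part: the absence of further missing-data methods here is not a fault in itself, and the FAS would be acceptable if described as what it is.

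A reader might go further in four ways that the documents do not support.

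- **That the primary ANCOVA is complete-case.** Reserving LOCF for sensitivity suggests it, but the article is silent on how a missing week-16 FPG is handled in the primary model.
- **That the primary and LOCF analyses err in the same direction, in favour of the drug.** LOCF can err either way: a patient who stops before the full effect carries forward a partial fall, and one who stops with worsening glucose carries forward a poor value. Whether carrying a drug effect forward is bias at all also depends on the estimand.
- **That 0.10 and 0.07 mmol/L measure bias in the primary result.** They concern LOCF alone, sit near the upper end, and cannot apply to patients with no value to carry forward.
- **That a mixed model for repeated measures would restore all randomised patients.** With baseline as a covariate, it gains no information from patients without a post-baseline FPG, which is the group at issue.

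Two points survive the defence, because the article states both: the population sentence contradicts itself, and LOCF is the prescribed default.

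**Conclusion.** The concern holds in a limited form. The contradiction is certain from the text. The weakness of LOCF as the default check follows from what it assumes and whom it cannot include. The size and direction of any actual bias cannot be derived. The illustrations, up to 0.10 and 0.07 mmol/L for LOCF and 0.04 to 0.12 mmol/L in either direction for FAS exclusions of 12% against 4%, rest on assumed loss rates and outcomes and show scale only. The matter should be corrected before the analysis plan is confirmed. It does not invalidate the design.

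**What to change.** 1. **Settle the primary set**, in one of two ways.
   - Define it as all randomised patients, as allocated, with multiple imputation of week-16 FPG (including patients with no post-baseline FPG) feeding the planned ANCOVA; or
   - call it FAS or modified intention-to-treat, delete the phrase about including all randomised patients, and add the all-randomised imputed analysis as a sensitivity analysis.
2. **State how a missing week-16 FPG is handled** in the primary model.
3. **Replace or supplement LOCF** with placebo-reference multiple imputation, a delta tipping-point analysis, or both, so that the missing-data assumption is actually varied.
4. **State whether expulsion cases**, including those unblinded in an emergency, stay in the primary set.

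The cost is revised wording, some extra programming and possibly slightly wider intervals. No new data are needed. Recruitment was still open when the article was written, and the analysis plan is to be confirmed before the first unblinding, so the change can be made blind to the results.
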